#### Treatment-as-usual control group

The TAU control group is implemented in two cooperating outpatient clinics. The responsible therapists are also psychotherapists in training who are under regular case supervision.

Treatment is based on psychotherapy guidelines [63] and current evidence-based practices for the treatment of depression in childhood and adolescence. No further restrictions with respect to duration or length are made. Family involvement is based on the current psychotherapy accounting rules of the German health care system (every 4th session).

#### Therapists training and adherence to the study protocol

All therapists are graduates in psychology or pedagogics and participate in a postgraduate training as child and adolescent psychotherapists in a university integrated outpatient clinic. As part of this training, they attend theoretical seminars and are supported by regular, high-frequency case supervision every fourth session. Consequently, all therapies in the study are implemented under this regular case supervision. In the intervention group (CBASP@YoungAge), the therapists participate in an additionally CBASP@YoungAge Workshop (ELB, ND) before initiating therapy. The treatment process is accompanied by regular additional CBASP@YoungAge case supervision. Supervision takes place every four weeks and is done by a licensed and CBASP-certified therapist (ELB). The therapists can discuss their cases during the supervision, review the process, and ask questions about the study procedure.

To ensure adherence to the protocol, we created a standardized checklist for data collection for each child/adolescent participating in the study. The study team review the checklists and remind the therapists either by text message (e-mail) or phone calls once a month to complete assessments with their patients in case of missing data. Every module closes with an adherence check that the study therapists complete at the end of each module. As part of the process evaluation, study therapists fill out a documentation form and report on the format, session length, participating persons, the module conducted, and important additional information after each session. The study team reviews all completed forms once a month and contacts the treating therapist in case of difficulties or non-adherence.

For organizational matters, and beyond the therapy implementation, a written study plan is made available to all study therapists. This document explains all study procedures (time points, documents) and the study coordinator (ND) clarifies questions and reviews all documents submitted by the therapists regularly.

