### Recruitment and procedure

Since the design is non-randomized, patients are consecutively recruited in the participating outpatient clinics. After initial appointments, therapists in the outpatient clinics identify and approach eligible patients based on the inclusion and exclusion criteria. They participate either in the CBASP@YoungAge treatment arm or in the treatment-as-usual control group (TAU). If screening indicates that the patient is eligible for participation and the family consents, complete study information is given to all participants, and written informed consent is obtained from the primary caregiver and participating child or adolescent.

Assessments are at baseline, post-treatment, and 6 months follow-up. During the treatment phase, a quantitative and qualitative orientated therapy process evaluation by therapist, patient, and caregivers is planned for every session, as is a quantitative evaluation of the general health index by patient and caregivers every 5th session. For detailed information on the study procedure, see Fig. 1 and for an overview of the actual study process and timeline Fig. 2.

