**Fig. 2 Fig2:**

Timeline of the study

The psychotherapeutic process is evaluated during treatment by the study therapists. If difficulties arise during treatment, the study therapists contact the study team in the appropriate outpatient clinic. The intervention or follow-up is discontinued if the caregivers or patients withdraw consent or a different treatment becomes necessary. The therapy process is also discontinued if the trial has to be unexpectedly canceled, or if the study coordinator decides it is necessary to discontinue, for example in case of adverse events. The risk management information below provides further information. The date and reason for discontinuation or drop-outs after screening will be documented.

After treatment completion, trained therapists will carry out regular post-assessments who were not involved in the treatment. Participants have to wait for at least 6 weeks before booster sessions are allowed when needed. If follow-up treatment (e.g., for comorbidities) appears to be necessary during booster sessions, that can be implemented as part of regular outpatient treatment, and will be documented (see Fig. 3 for the study flow).

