### Randomization, allocation concealment, and blinding

Assignment to the two study arms is non-randomized and the allocation is not blinded. The pre- and post-assessments will not be blinded, but rather done by trained psychotherapists who are independent and did not provide treatment in either of the study arms to the respective families.

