### Outcomes

Assessments are at pre-treatment (T1), post-treatment (T2) and follow-up at 6 months (T3) (see Fig. 1 for overview). Assessments are face-to-face (clinical interview) or paper-pencil questionnaires and filled out by index patients and/or their caregivers/significant others.

Primary outcomes are, first, the feasibility of the CBASP@YoungAge treatment program. This includes both practicability in the outpatient setting for therapists and suitability for patients and family members, primarily measured by continuous process evaluation (therapists, patients, parents), therapist adherence, patient dropout rate, and recruitment rate during the study and treatment. Second, change in depressive symptomatology between pre- and post-assessment is a primary endpoint, with change measured by the clinical interview (child DIPS, parent or child version) and the Mood and Feelings Questionnaire (MFQ).

Secondary outcomes are the interpersonal behavior between caregiver and children (Impact-Message-Inventory for children and adolescents, IMI@YA), the global health of both caregivers and participating children (KIDSCREEN; Positive mental health questionnaire, PMH), parents' mental health (Brief-Symptom-Inventory, BSI), and parenting quality (Parenting Questionnaire, EFB).

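### As worded, the monthly missing-data reminder sends missed assessments back to the treating therapist, which conflicts with the promise of independent pre- and post-assessment

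*Protocol article*

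**What the plan says.** All references are to the protocol article.

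- **Who assesses.** Under *Randomization, allocation concealment, and blinding*, pre- and post-assessments are unblinded but "done by trained psychotherapists who are independent and did not provide treatment in either of the study arms to the respective families". The text under Fig. 2, in *Recruitment and procedure*, repeats this for the end of treatment: "trained therapists will carry out regular post-assessments who were not involved in the treatment".
- **Who follows up missing data.** Under *Therapists training and adherence to the study protocol*, the study team reviews a per-patient checklist ("we created a standardized checklist for data collection for each child/adolescent participating in the study") and contacts the therapists by e-mail or phone "once a month to complete assessments with their patients in case of missing data".
- **What counts as an assessment.** *Outcomes* states: "Assessments are at pre-treatment (T1), post-treatment (T2) and follow-up at 6 months (T3". It adds that these are face-to-face clinical interviews or "paper-pencil questionnaires and filled out by index patients and/or their caregivers/significant others". *Recruitment and procedure* also uses the word for baseline, post-treatment and 6-month follow-up. The session measures get another name: a "therapy process evaluation by therapist, patient, and caregivers is planned for every session".
- **What is at stake.** Change in depressive symptoms from pre to post, measured by the Kinder-DIPS and the MFQ, is a primary endpoint (*Outcomes*).

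**The concern.** Independent assessment is the trial's stated protection against bias from the lack of blinding: the limitations paragraph of the *Discussion* relies on clinical evaluations not being done by the study therapists. A missing-data rule that leads back to the treating therapist, without exception, opens a route around that protection.

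Two consequences would matter if the rule were followed literally. At T2, an interview or self-report form could be completed with the person whose treatment it evaluates, which invites favourable answers. At T1, a questionnaire recovered late could already reflect early treatment. If patients improve early, pre-post change would then be understated and the baseline value would no longer be a pre-treatment one.

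Arm is also fully tied to clinic: Marburg delivers the intervention, Bochum and Landau deliver usual treatment. Any difference between clinics in how often this route is used could not be separated from the treatment effect.

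**Working it through.** The article states no figure on this point, so there is nothing to reproduce. The check is a comparison of texts, plus one illustrative calculation.

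**Step 1: who is reminded.** The adherence section addresses therapists about patients who are theirs. In that section the therapists are those delivering treatment and receiving case supervision. The natural reading is the treating therapist.

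**Step 2: what they are asked to complete.** The sentence names no time point and no instrument, and the checklist behind it covers data collection for each participant. In *Recruitment and procedure* and *Outcomes*, the word *assessments* denotes T1, T2 and T3, while session measures are mostly called evaluation. The same adherence section gives the therapists' session documentation forms a separate monthly review. Both facts weaken a reading confined to process paperwork.

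**Step 3: where the rules collide, by measure.**

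| Measure | Independence stated? | Exposed by the reminder as worded? |
|---|---|---|
| T1 Kinder-DIPS | Yes | No: it decides inclusion (*Participants and sample size*), so it exists at entry |
| T1 questionnaires, including MFQ | Yes, if part of the pre-assessment | Possibly: late recovery is neither stated nor excluded |
| T2 Kinder-DIPS | Yes | Yes: this is where independence of the rater matters most |
| T2 MFQ | Yes, if part of the post-assessment | Yes: self-report, so the issue is the therapist's presence, not the rating |
| T3 measures | Not named in the two independence statements | Yes, but without a direct contradiction of those statements |

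**Step 4: how late a form could be.** One monthly cycle is 30.4 / 7 = 4.3 weeks. *CBASP@YoungAge intervention* gives one to three sessions a week, so a cycle spans 4.3 × 1 ≈ 4 to 4.3 × 3 ≈ 13 sessions of a 20 to 30 session programme. This is the longest delay within one cycle, for a form missed just after a review. It applies to the intervention arm only, since no session frequency is given for usual treatment. It shows that late recovery could fall well inside therapy. It does not measure bias.

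**The case against.** The best defence is that the reminder sentence stands among text on adherence during therapy, next to module adherence checks and session documentation. It may therefore concern only the in-treatment forms, or mean only that the therapist prompts the family. A loose general sentence is ordinarily read together with the explicit independence rules, not as overriding them. This stands in part: the conflict lies in the wording, and actual practice is not shown. But the article's own use of the key word points the other way, and nothing in the text limits the sentence.

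Second, the questionnaires are self-report, so a therapist who hands over an MFQ does not rate it. This stands. For the MFQ the concern is the therapist's presence; loss of rater independence applies to the T2 Kinder-DIPS.

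Third, T2 follows the end of treatment, and booster sessions must wait at least 6 weeks. A reminder at about 4.3 weeks would therefore find no scheduled session in which to complete a form. This makes the T2 route less likely but does not close it, because the reminder itself asks the therapist to act.

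Fourth, the article mentions a written study plan covering time points and documents, which is not shown and may set windows and routing. The absence of such detail is accordingly not the point. The point is that two statements in the article disagree.

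A reader might go further and infer that late T1 forms are filed as pre-treatment, or that missed session ratings are filled in from memory in front of the therapist being rated. The article says neither.

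**Conclusion.** The reminder rule, as worded, conflicts with the two statements that pre- and post-assessments are done by non-treating psychotherapists, and the sections must be reconciled. The conclusion rests on reading *assessments* as the article itself uses the word.

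The exposure is limited to the T2 Kinder-DIPS and questionnaires, the T1 questionnaires and, without a direct contradiction, T3. The late-T1 consequence is a possibility left open, and its direction (understated change) assumes early improvement. Any effect on the group comparison further assumes that the ANCOVA adjusts for the baseline score, since the article does not list its covariates.

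No size of bias can be given, because the number of forms recovered this way is unknown. A reader might divide the 13 sessions at the highest frequency by the programme length (13/30 = 43%, 13/20 = 65%) and take that as the distortion. The documents do not support this: it is a share of sessions in the longest delay at the highest frequency, not an effect on any outcome. With 22 patients planned per arm, a few affected forms could still matter, and the correction is cheap.

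**What to change.** Amend the reminder sentence under *Therapists training and adherence to the study protocol*, and the matching study plan and checklist, to say that:

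1. monthly reminders to treating therapists cover in-treatment process forms only;
2. missed T1, T2 and T3 interviews and questionnaires are followed up by the independent assessors or the study team, not by the treating therapist;
3. every T1 questionnaire carries its completion date, and one dated after the first treatment session is flagged and not used as baseline without a sensitivity analysis that sets it to missing.

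Reporting the number of flagged forms by arm would show whether the problem arose at all.

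The cost is a change of wording and some extra follow-up work for assessors and coordinator who are already in place. The downside is a few more missing values, for which *Statistical analysis* already plans random-forest imputation. When the article was published in July 2022, recruitment was still open and follow-up was due to run to the end of July 2023, so the change could still have protected later T1, T2 and T3 data.

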### Outcomes

Assessments are at pre-treatment (T1), post-treatment (T2) and follow-up at 6 months (T3) (see Fig. 1 for overview). Assessments are face-to-face (clinical interview) or paper-pencil questionnaires and filled out by index patients and/or their caregivers/significant others.

Primary outcomes are, first, the feasibility of the CBASP@YoungAge treatment program. This includes both practicability in the outpatient setting for therapists and suitability for patients and family members, primarily measured by continuous process evaluation (therapists, patients, parents), therapist adherence, patient dropout rate, and recruitment rate during the study and treatment. Second, change in depressive symptomatology between pre- and post-assessment is a primary endpoint, with change measured by the clinical interview (child DIPS, parent or child version) and the Mood and Feelings Questionnaire (MFQ).

Secondary outcomes are the interpersonal behavior between caregiver and children (Impact-Message-Inventory for children and adolescents, IMI@YA), the global health of both caregivers and participating children (KIDSCREEN; Positive mental health questionnaire, PMH), parents' mental health (Brief-Symptom-Inventory, BSI), and parenting quality (Parenting Questionnaire, EFB).

#### Demographic data

For patients, demographics include information on sex, age, place of birth, spoken languages, siblings, school and social factors like friendships, and sports club affiliation. For caregivers/significant others we assess sex, age, education level, and marital status as well as socio economic status (SES). We also screen for any abnormalities in early development or during pregnancy.

#### Diagnostic Interview for Mental Disorders for Children and Adolescents (Kinder-DIPS)

The Kinder-DIPS [52] is a structured interview for the assessment of mental disorders and behavioral problems in children and adolescents that can be completed with the child/adolescent or their caregiver. The diagnostician decides with whom the interview will be conducted. In most cases, children older than 12 years of age can participate the interview themselves. If there is no clear result, the interview can also be conducted with both parties, i.e., caregiver and child. The Kinder-DIPS provides a diagnostic classification according to DSM-5 [51] or ICD-10.

The Kinder-DIPS contains both open and closed questions. Although both the wording and order of the questions are clearly specified, it is possible for the interviewer to ask clarifying follow-up questions. The interrater reliability of the parent and child versions of the Kinder-DIPS is highly satisfactory with respect to major diagnostic categories, and for ruling out mental disorders [64].

#### Impact Message Inventory (IMI) for children and adolescents (IMI@YA)

The IMI@YA is an adaptation of the German version of the IMI [65] for children and adolescents ([name], [name], [name]: Capturing impact messages in parent - child interactions: Adaption and Validation of the Impact-Message-Inventory, in preparation). It is an interpersonal questionnaire designed to represent the various dimensions of the Kiesler-Circle that is administered to assess interpersonal characteristics by others [66]. This instrument assesses the interpersonal behavior between caregiver and child, that is, the children provide their perception of their parents’ interaction behavior, and vice versa.

The IMI@YA contains 64 items with eight items per scale to be answered on a 4-point Likert Scale from “not at all” (0) to “very much so” (4). The eight scales represent the octants of the Kiesler-Circle read counterclockwise from the top of the circle are called dominant, hostile dominant, hostile, hostile submissive, submissive, friendly submissive, friendly, and friendly dominant. Cronbach’s alpha ranges between .45 (friendly submissive) and .85 (friendly) in a non-clinical sample ([name], [name], [name]: Capturing impact messages in parent - child interactions: Adaption and Validation of the Impact-Message-Inventory, in preparation).

#### Mood and Feelings Questionnaire (MFQ)

The MFQ detects clinically relevant symptoms of depression in children and adolescents. For the current study, we use the German version of the MFQ that measures depressive symptoms on a 3-point Likert scale with 0 = “not true”, 1 = “sometimes” and 2 = “true” (Universität Ulm, 2015 based on [67]). The MFQ demonstrates excellent reliability scores (US sample: self: α = .89, caregiver α = .91; German sample: self: α = .93, caregiver: α = .90) [68].

#### KIDSCREEN

The KIDSCREEN [69] assesses children’s and adolescents’ subjective health and well-being. The KIDSCREEN is a self-report measure for healthy and chronically ill children and adolescents aged 8 to 18 years. It is available in different versions. We use the 27-item version in for pre-, post-, and follow-up assessments, and the 10-item short version for therapy process evaluation every 5th session. The KIDSCREEN-27 is based on the 52-item full version and provides detailed profile information on five Health-Related Quality of Life (HRQoL) dimensions. The KIDSCREEN-10 Index provides a global HRQoL score for monitoring and screening purposes and takes 5 min to fill out.

The KIDSCREEN instruments are available in child, adolescent, and parent versions, and have been translated and adapted for use in several languages. A total score can be calculated, and T-values and percentages are available for each country stratified by age and gender. Cronbach’s alpha ranges between .79 (physical wellbeing) to .84 (psychological wellbeing); Cronbach’s alpha is .82 for the ten-item version [70].

#### Positive Mental Health Scale (PMH)

The Positive Mental Health Scale (PMH-scale [71]) measures positive mental health with a brief, unidimensional, and person-centered questionnaire. The scale consists of nine items rated on a Likert scale from 1 = “not true” to 4 = “true”. The internal consistency is about .93 for all groups together and .82 in the retest sample. The PMH-scale’s internal consistency is high and similar across different samples [71]. This instrument is completed by the caregivers.

#### Brief symptom inventory (BSI)

The Brief Symptom Inventory [72] consist of 53 items, and is a questionnaire for documenting subjective impairment caused by physical and especially psychological symptoms. Based on the Symptom Checklist SCL-90-R, the items assign to nine scales (somatization, obsessiveness, insecurity in social contact, depressiveness, anxiety, aggressiveness/hostility, phobic anxiety, paranoid thinking, psychoticism) and enable three indices of global distress to be calculated. The internal consistencies of the nine scales range from .70 (Psychoticism) to .87 (depressiveness). Gender- and age-specific norm values are available. This instrument is also completed by the caregivers.

#### Erziehungsfragebogen (EFB)

The Parenting Questionnaire (EFB) [73] is the German version of the parenting scale [74]. The EFB is a self-assessment scale of parenting behavior in situations when the child is to be disciplined. Its three scales (overreaction, laxness, and verbosity) and a total score can be analyzed. The internal consistencies of the overreacting and laxness scales and of the total score are acceptable to good (.59–.80). The verbosity scale’s values were low [73].

#### Therapy process evaluation

An evaluation is implemented for continuous therapy support by relying on the MRC guidance [75] on how to conduct process evaluations of interventions. This consists of short questionnaires to be completed by everyone involved after each therapy session, and of short questionnaires (KIDSCREEN-10, PMH) after every fifth therapy session. As the study’s target population are youth patients with depression and stressful family relationships, process evaluation is as short and practicable as possible. We therefore limit ourselves to documenting the change in symptoms compared to the beginning of therapy (subjective rating of 1 = “worse” to 10 = “better”), the satisfaction with the actual therapy session (subjective rating 1 = “dissatisfied” to 10 = “satisfied”) and ask for qualitative descriptions of other comments. These open-ended questions are not intended to be a substitute for careful qualitative analysis, but allow us to capture unanticipated therapy events from the participants' perspective not yet included in the protocol. The aim of this first step in the process evaluation is to check the intervention’s feasibility and establish the course of symptoms over time as well as the participants’ general health-related well-being.

In the second step, we focus specifically on the structure of each therapy session by asking therapists how they conduct each session. For that purpose, they fill out a session log sheet after each session. Here they indicate how long the session lasted, who participated, which techniques they applied, and whether the session was conducted online or face-to-face. This will help us understand the feasibility and implementation of each module and session, and optimize the program after this study.

Furthermore, we focus specifically on the intervention’s structure. Have the therapists implemented it correctly? The therapists fill out a session protocol sheet after each session for just this reason. Here they indicate the frequency and duration of the sessions, who participated, and whether the appointments were implemented online or live. This helps us better understand the feasibility and implementation of each module and to identify potential structural differences related to specific modules.

